#### Health care utilization

Questions from the German version of the European Health Interview Survey (GEDA/EHIS 2014/2015) [46] are used to assess the type of insurance, number of consultations with a General Practitioner (last 12 months), number of consultations with a specialist (last 12 months), visits to the emergency room (last 6 months), and overnight hospital stays (last 12 months). Additionally, we assess disease-specific health care utilisation (past 6 months) as part of the SST.

#### Primary care continuity

Primary care continuity is related to a range of health outcomes including reduced mortality, lower health care costs, and hospitalisations [47, 48]. We use items on longitudinal continuity of care (care site and provider duration) from a continuity of care model used in the National Health and Health Services Use Questionnaire (NHHSUQ) [49]. The items assess the most frequently visited health care site, duration of care at care site, presence of a specific care provider, duration of care from care provider and changes in care provider in the last 12 months.

#### Patient activation of care

Patient activation refers to the knowledge, confidence, skills, and abilities of patients to manage their own care. Patient activation is a known predictor for a range of health and treatments outcomes, health behaviours, as well as lower hospitalization rates and visits to A&E [50]. Patient activation is assessed using three items as used in the SST: patient perceived knowledge about their own condition (“very little”, “something”, “a lot”), confidence in management of own physical ailments (“not at all confident”, “a little confident”, “somewhat confident”, “quite confident”, “extremely confident”), and problems in understanding information about their own health (“always”, “often”, “sometimes”, “occasionally”, “never”) [10].

#### Use of medication

As many older patients have multimorbid health needs and require polypharmacy, we ask for the use and number of prescription drugs taken regularly.

#### Smoking behaviour

As smoking is a risk factors for many health outcomes, tobacco use is evaluated using three questions from the GEDA/EHIS 2014/15 questionnaire [46] on current use of tobacco products, past tobacco use and total duration of tobacco use in years.

### Loneliness & wellbeing

#### Loneliness

Loneliness is linked to outcomes in mental health, general health, well-being, physical health, sleep and cognition [51]. We use adapted and abbreviated versions of the UCLA Loneliness Scale [52]. We employ an 8-item version, adapted from the revised UCLA Scale (Version II), with a 5-point response scale, to allow for comparison with other ageing studies (BASE II Berlin Ageing Study) [53].

#### Risk of social isolation

The Lubben Social Network Short Scale is used as a screening tool to identify persons at risk of social isolation. The six-item scale assesses social ties with family and friends and has been used and validated in older populations in a European and Singaporean context [54–56]. Social Isolation has been linked to higher mortality among other health outcomes [57, 58].

#### Control beliefs (Berlin survey only) & resilience (Singapore survey only)

Both control beliefs and resilience are associated with wellbeing in older age [59, 60]. We use three items on internal locus of control as used in the BASE II study in Germany [61]. Participants are asked how much the following three statements apply to them on a scale of 1 = not at all applicable to 5 = very much applicable: “I can determine the good things that are happening in my life”, “If I get what I want, it is usually because I have done a lot for it myself”, “I can influence the good and beautiful things in my life myself”.

In Singapore, resilience is measured using the Brief Resilience scale (BRS) [62]. The six-item BRS asks participants to what extent they agree (five response options from strongly agree, disagree, neutral, to agree and strongly agree) with statements about bouncing back after hard times, making it through and recovering from or getting over from stressful events.

#### General life satisfaction

To determine general life satisfaction participants are asked: “Overall, how satisfied are you currently with your life?” and given a 10-point response scale. 0 = completely unsatisfied and 10 = completely satisfied [63].

### Mobility

#### Life space assessment

The University of Alabama at Birmingham Study of Aging Life-Space Assessment (UAB-LSA) measures mobility of older adults in their home and community [64]. It has been validated and is associated with a range of outcomes, including limitations in activities and instrumental activities of daily living, functional mobility and self-rated health [15, 16].

#### Functional assessment: daily activities, assistive devices & Gali score

We measured functional capacity among participants by assessing the extent to which health- or physical limitations affected the ability to independently perform different everyday activities (Basic and Instrumental Activities of Daily Living). The GALI Score (Global Activity Limitation Index) [65] is used to determine the overall (6 month) limitations in everyday activities due to health conditions. The presence of limitations reported on the GALI are used for population segmentation as per the SST framework, for example, in classifying participants with chronic conditions as having symptoms that interfere with or restrict usual function even if they are not necessarily hospitalized for that condition.

### Living environment

#### Type of housing and duration of living in current housing

Participants are asked in what type of housing they live (e.g. rented, owned, apartment, etc.). The answer choices are adapted to the local Singapore/Berlin housing context. Participants are then asked how long they have approximately lived in the current housing (in years/months).

#### Neighbourhood social cohesion

Self-perceived neighbourhood cohesion is measured using 7-items, which have been used in the Health and Retirement study (HRS) [66]. Participants are asked to rate the 7 statements about the neighbourhood regarding the community, trustworthiness, safety, cleanliness, friendliness, helpfulness, attractiveness using five answer categories (“strongly disagree, disagree, neither agree/disagree, agree, strongly agree”). Self-perceived neighbourhood social cohesion has been found to be associated with a lower risk for a range of physical and mental health outcomes, e.g. myocardial infarction, falls, anxiety and depression [67–69].

#### Environmental age-friendliness

Age-friendliness of the environment is a strong predictor for quality of life and loneliness in older adults [70]. The Age-friendly environment Assessment Tool (AFEAT) is a reliable, validated instrument, that has been developed based on the WHO age-friendly environment checklist [70]. It assesses individual perceptions of the individual environment (e.g. accessibility and availability of services, medical care, public transportation etc.) using 10-items on a 5-point Likert scale [70]. We use an adapted version of the AFEAT questionnaire with some additional items. In Singapore, the module is expanded, with the aim of collecting data on the perception of additional context-specific services: e.g., whether neighbourhood centres such as Active Ageing Centres (a major public policy initiative aimed at older adults in Singapore) had activities and events of interest to participants, or the ease with which participants are able to read/understand information about programmes and services on posters, flyers, notice boards, etc.

#### Access to green spaces

To determine subjective access to green spaces, a 5-point Likert scale statement (“I live close to public green spaces such as parcs, gardens or woodlands”) is added in the same format as the AFEAT items.

### Socioeconomic measurements

To assess sociodemographic variables a range of standardized questions are used. The following socioeconomic characteristics are measured: gender, household size, marital status, number of living children, native language, migration background (Berlin only), ethnicity (Singapore only), East/west German background (Germany only), educational attainment, income sufficiency, and housing type (Singapore only; housing type has been found in previous research to be proportional to household income and frequently used as a proxy for household socioeconomic status [71]). In the German version the majority of questions are based on the Diversity Minimal Item Set (DiMIS) [72].

The MacArthur Scale of Subjective Social Status [73] is selected as a measure for individual socioeconomic status (SES) as it highly correlated with more objective multidimensional SES measures, that tend to yield high levels of missing values in surveys, e.g. on questions on income [74].

### Functional assessments

#### Cognitive status

Cognitive status is assessed using a paper-and-pencil digit symbol substitution test (DSST). The DDST is a valid and established instrument for cognitive disfunction, that is quick to implement [75]. DDST is a strong predictor for mortality and functional outcomes [75, 76].

#### Hand grip strength and walking speed

Hand grip strength and walking speed are assessed as part of the criteria for frailty. Unless any counterindications are present, the participant’s hand grip strength is determined twice for each hand using a standardized dynamometer. For walking speed, the time it takes participants to cover a marked distance of 2.5 (using a walking aid if necessary) is stopped. The walking speed measurements are taken at a clear and level space (uncarpeted, if possible) of 2.5 m at the participants homes. Start and end points are measured out by the interviewer and marked with masking tape. Measurements are taken twice and the average of the two times is taken as a participant’s walking speed.

### Other data sources

The survey data will be merged with openly available geospatial data from sources such as Open Street Map (OSM), or datasets from the Berlin Senate’s Geodata Portal. Among the data used will be Points-of-interest from OSM, which will be filtered and classified into categories relevant to the elderly. Additionally, we will model walkability of the target neighbourhoods with a focus on recreational use of urban green spaces (UGS), using two indices, namely the local significance (LS) and detour index (DI). LS will be used as to model recreational flows and potential overcrowding effects of UGS, while DI will serve as a proxy for barriers that elderly people may encounter on their ways to UGS. All data will be modelled in 300 m, 500 m and 1000 m network distances around all residential buildings in the target LORs and later matched via address to the survey data to fulfil data protection requirements.

## Qualitative data collection and analysis

We will conduct and analyse *n* = 50 qualitative walking interviews with older adults to understand their usage patterns, activities and perceptions of physical and other barriers encountered in urban green spaces and streets.

First, the Berlin team will prepare the qualitative interview guidelines and share the guidelines with the Singapore team. The interview guidelines will be tested. We aim to randomly select participants from contrasting neighbourhoods to gain a diverse range of perspectives. Whenever possible and always in agreement with the persons approached, we intend to conduct these interviews as walking interviews through the study site alongside our interviewees on a route chosen individually by the participants according to their preferences, adapting our approach based on their mobility. Interviews will be transcribed and pseudonymised. Interview transcript will be analysed qualitative with a coding process oriented towards the grounded theory paradigm.

## Quantitative data analysis

After data cleaning, we will conduct both cross-sectional and longitudinal analysis of the data. We will first examine missing values and if there is a need for multiple imputation. We will then conduct descriptive data analyses and regression analyses taking the multilevel type of the data into account. Sensitivity analyses will be conducted to ensure the robustness of our results.

## Triangulation of results

We will triangulate the quantitative and qualitative results on neighbourhood level and a general level. In joint triangulation workshops researchers will bring their results together discussing the results and topics from an interdisciplinary mixed methods perspective.

## Discussion

### Strengths and limitations of the study

The mixed-methods design, which incorporates multiple study sites and data sources, enables an examination of the various dimensions of ageing well from a range of perspectives. The large sample survey provides a substantial data set for quantitative analysis and can be linked to objective geographical geographic indicators at the neighbourhood or street level. The large dataset allows for pooled analyses of the sample using multilevel analysis to account for differences in the study sites as well as comparative or stratified analyses, where deemed relevant, to identify differences between or within the subsamples. As the samples are drawn at random from the registry offices at both study sites, the pool of potential candidates reflect the populations aged 65 or older of the respective neighbourhoods in terms of the socioeconomic characteristics including gender, age distribution and ethnic or cultural diversity. By opting for home visits (including visits in nursing homes), older people with reduced mobility are more likely to participate and the burden of participation is reduced. Furthermore, the qualitative data offer a more subjective insight into the needs of individuals and their perceptions of their neighbourhoods, which may not be fully captured in the standardised interviews.

The longitudinal design can capture short-term changes in the participants health and social needs within 12 months. The study has the potential to be expanded into an ongoing longitudinal study with multiple follow-ups in the long term.

The study also comes with several methodological limitations. Due to the differences in context and administrative regulations, the methodology and questionnaires had to be adapted slightly between Singapore and Berlin with regards to sampling, data collection and sociodemographic measures. Secondly, individuals who are advanced in age, experience significant health limitations, or express reservations about a home visit are less likely to participate in the study. Additionally, at the Berlin study site, the interviews are conducted in German, which limits participation from those who do not have sufficient German skills to complete the interview.

The selection of three to five neighbourhoods in each city may limit the generalisability of the results, however, the use of many standardised instruments allows the results to be compared with other cohort studies of ageing.

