#### Singapore

In Singapore, studies of older adults have often focused on public housing residents and detailed the experiences of those living in more mature housing estates. A key contribution of this project will therefore be the inclusion of and comparison between participants in both public and private housing and mature and non-mature estates. The following criteria were considered for selecting the neighbourhoods for the study in Singapore: (1) a sizeable older adult population, (2) mix of relatively older and newer housing estates, i.e., those that developed in different decades since the 1950s to the mid-1990s. Five planning areas were chosen in Singapore: Tampines, Sengkang, Clementi, Ang Mo Kio and Kallang. Within each planning area, one sub-zone with a substantial proportion of older adults to the total population was selected. Planning areas, currently 55 in number, are used in Singapore primarily as development guide plan (DGP) areas, i.e., the level at which the statutory board, Urban Development Authority, draws up detailed land-use plans [40]. The study will obtain a random sample of 5,700 potential residential addresses across the sub-zones from the Singapore Department of Statistics. The sample frame from which addresses were chosen were residential addresses with at least one Singapore citizen or permanent resident aged 65 years and older. The distribution of addresses across housing types (i.e., government-built or Housing Development Board [HDB] 1–2 room apartments, 3-room apartments, 4-room apartments, 5-room or larger apartments) in the sample was proportional to the distribution of housing types in within each sub-zone.

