### Selection of potential participants

#### Berlin

A random sample of 5,250 registered adults aged 65 or older in the four planning areas is drawn from the Berlin registration office. Participants receive an invitation letter explaining the study objectives, the participation process, the privacy policy, and a copy of the informed consent form. If more than one person per household is selected in the random sample, each receives an individual invitation to participate. Participants who do not wish to take part in the study can opt out by e-mail or telephone. Those who do not opt out receive a second letter with an appointment for the home visit, with another opportunity to opt out of the study or choose another interview date by telephone or e-mail. On the day of the home visit, participants are given the opportunity to participate then and there, to participate at another time, or to refuse to participate. Those who refuse are considered active refusals. Those who cannot be reached on the day of the announced site visit, receive at least one more letter with an announced home visit. Those who do not respond to any letters or home visits are considered passive refusals at the end of data collection. If participants agree to take part in the survey, the eligibility criteria (see Table 1) are checked. The same eligibility criteria apply for follow-up. Persons who move to a different neighbourhood between baseline and follow-up are only included if they move to a neighbourhood that is part of the study in the same district. All interviews are conducted in German.

**Table 1 Tab1:** Inclusion and exclusion criteria for each study site

Inclusion criteria	Exclusion criteria
Min. 65 years of age (Berlin + Singapore), Max. 95 years of age (Singapore)	No written consent provided (Berlin + Singapore)
Registered resident in one of the selected neighbourhoods in Berlin/Self-reported non-temporary resident of an address in the Singapore sample	Cognitively not capable to understand the written consent form (Berlin)/Fewer than 5 correct answers on Abbreviated Mental Test (Singapore)
Written consent provided (Berlin + Singapore)	Linguistically unable to participate in the survey (Berlin + Singapore)
Citizen or permanent resident (Singapore)	Participant has a legal guardian (Berlin)

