#### Singapore

The inclusion criterion for participants in the study in Singapore first stipulates that a participant should be among the regular residents of the address in the sample (i.e., they should not be visitors or living at the address temporarily for any reason), be a Singapore citizen or permanent resident, and be aged 65–95 years. The specification of an upper age was mandated by the NUS Institutional Review Board.

During a visit to the address, an interviewer will first seek to prepare a list with the initials of all such individuals living at that address, by asking any adult household member with the exception of domestic helpers who are unlikely to provide this information to interviewers. At that time, the interviewer will ask if any of the listed older adults is unavailable or unable to answer the survey questionnaire, and if case of any affirmative responses ascertain if this is the case because he/she is (i) unable to hear, or unable to speak, or has a chronic physical or mental illness or disability which would prevent him/her from being able to respond to a survey questionnaire on their own, or (ii) currently admitted to a hospital, nursing home, hospice, or another institution for health or other reasons, and unlikely to be available for an interview during the study period. Such individuals are deleted from the list. At addresses where two or more older adults remain on the list, the interviewer will first use a random sequence generator (available gratis on https://www.random.org/) and assign each remaining individual in the list a serial number in the same sequence as generated. Then, the interviewer will use the true random number generator (on the same website) and specify the number of the older adults on the list. The random number generator will yield one of the serial numbers, and this individual is therefore the randomly selected potential participant. This process ensures that in addresses where more than one older adult is eligible and able to participate in the study, the selection of one potential participant is done at random.

Subsequently, the selected potential participant is administered a cognitive status test. If the selected potential participant answers five or more questions correctly from the ten-item Abbreviated Mental Test– Singapore, a criterion that has been used previously in surveys administered with community-dwelling older adults [41], he/she is deemed eligible to continue [42].

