If a selected potential participant refuses to participate in the process outlined above or subsequently expresses unwillingness to participate in the study, a replacement potential participant is not chosen. Similarly, if an adult household member refuses to provide the initial information that allows interviewers to list eligible older adult residents at an address or disallows the interviewer from speaking to or contacting the selected potential participant, the study deems that household as having refused participation in the study. For reasons of propriety, the interviewer will not seek to speak to another adult household member at that address or visit it again. The interviews are conducted in one of the four official languages English, Mandarin, Malay and Tamil, depending on the participants preferences and abilities.

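### The article describes both sites as random registry samples reflecting the 65+ population, but Singapore draws addresses and then one older adult per address, so sole listed older adults are over-represented among those selected

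*Protocol article*

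**What the plan says.** Under *Strengths and limitations of the study*, the article treats the two cities alike: "As the samples are drawn at random from the registry offices at both study sites, the pool of potential candidates reflect the populations". The sentence goes on to name socioeconomic characteristics, among them gender, age and ethnic or cultural diversity.

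The design sections describe two different procedures.

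- **Berlin** (*Selection of potential participants*): 5,250 registered persons aged 65 or older are drawn from the registration office. "If more than one person per household is selected in the random sample, each receives an individual invitation to participate".
- **Singapore** (*Selection of neighbourhoods for data collection*): "The study will obtain a random sample of 5,700 potential residential addresses across the sub-zones from the Singapore Department of Statistics". The frame consists of "residential addresses with at least one Singapore citizen or permanent resident aged 65 years and older", and the sampled addresses are spread over housing types in a way "proportional to the distribution of housing types in within each sub-zone".
- **Singapore** (*Selection of potential participants*): the interviewer lists the older residents and removes those unable or unavailable to take part. A random number generator then settles, "in addresses where more than one older adult is eligible and able to participate in the study, the selection of one potential participant". If that person refuses, "a replacement potential participant is not chosen".

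*Quantitative data analysis* mentions a check of missing values, possible multiple imputation, descriptive analyses, multilevel regression and sensitivity analyses. It does not mention selection weights. The limitations acknowledge that sampling differs between the cities, but call the adaptation slight and do not mention unequal selection probabilities.

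**The concern.** A random draw of persons gives each older adult in a neighbourhood the same chance of selection. A random draw of addresses followed by one person per address does not: someone who shares the address with another listed older adult has half the chance of someone who is the only one listed. The Singapore addresses do not come from a registry office, and the selected persons do not mirror the 65+ population without a correction. The sentence asserts both properties for both cities.

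Household composition is plausibly related to loneliness, one of the study's three dimensions, and to social isolation, which is measured at both sites. The article foresees pooled analyses and, where relevant, comparisons between the subsamples. The distortion arises in one city only, so it would not cancel in an unweighted contrast. A reader or analyst who takes the sentence at face value would see no reason to weight, or to keep the number of listed older adults in the data set.

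**Working it through.** **The plan's own figure.** *Sample size* gives 3 × 350 = 1,050 for Berlin and 5 × 210 = 1,050 for Singapore. Both reproduce. The implied yields are 1,050/5,250 = 20.0% and 1,050/5,700 = 18.4%. The target is not in dispute.

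**Selection probability in Singapore.** P(person) = P(address) × 1/k. Addresses are allocated by housing type, not by their number of older residents, so within a sub-zone and housing type P(address) does not rise with k. A person's chance is therefore proportional to 1/k: one half at k = 2 and one third at k = 3, relative to k = 1. The direction of the imbalance holds for any household mix that contains addresses with more than one listed older adult.

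**Size of the imbalance (assumed inputs).** The documents do not give the household mix. Let a be the share of addresses with one listed older adult, and let the rest have two.

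- Share of sole listed older adults in the unweighted sample: a
- Share among persons: a/(2 − a)
- Kish design effect of weighting by k: [a + 4(1 − a)] / [a + 2(1 − a)]²
- Effective n: 1,050 / design effect

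| a (assumed) | Share among persons | Excess in sample (points) | Design effect | Effective n |
|---|---|---|---|---|
| 0.4 | 25.0% | 15.0 | 1.094 | 960 |
| 0.5 | 33.3% | 16.7 | 1.111 | 945 |
| 0.6 | 42.9% | 17.1 | 1.122 | 935 |
| 0.7 | 53.8% | 16.2 | 1.124 | 934 |
| 0.8 | 66.7% | 13.3 | 1.111 | 945 |

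Example for a = 0.6: 0.6/1.4 = 0.429, and (0.6 + 1.6)/1.4² = 1.122.

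**Effect on a mean (assumed inputs).** Let d be the outcome difference, in SD, between sole listed older adults and the others. The shift is [a − a/(2 − a)] × d. The standard error of a simple 1,050 v 1,050 comparison is √(2/1,050) = 0.044 SD, ignoring clustering.

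- Smallest non-zero case, a = 0.8 and d = 0.1: shift 0.013 SD, about 0.3 SE.
- Largest case, a = 0.6 and d = 0.5: shift 0.086 SD, about 2.0 SE.
- d = 0: no shift.

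**Effect on a prevalence (assumed inputs).** Take a = 0.6, with loneliness at 30% in sole listed older adults and 15% in the others.

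- Among persons: 0.429 × 0.30 + 0.571 × 0.15 = 21.4%
- Unweighted: 0.6 × 0.30 + 0.4 × 0.15 = 24.0%
- Shift: +2.6 points. The one-city SE at p = 0.22 is √(0.22 × 0.78/1,050) = 1.28 points, so the shift is about 2.0 one-city SEs. For the city contrast the SE is 1.28 × √2 = 1.8 points, so the shift is about 1.4 SE.
- With 30% v 20% instead: 26.0% against 24.3%, a shift of +1.7 points.

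**The case against.** Four arguments on the other side have weight.

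1. **The article does not say the analysis is unweighted.** Its analysis section is a few sentences long, and survey weights are normally set out in a fuller plan. This stands: the absence of weights is not itself an error, and any bias is conditional on their not being used.

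2. **The sentence is a discussion remark about a pool of candidates and lists characteristics other than household composition.** This stands in part. All older residents of the sampled addresses could be called such a pool, and the design sections describe the Singapore procedure fully. But the stated source is still wrong for Singapore, and the persons actually selected do not inherit the claimed property. Choosing one person per address could also shift age and gender, though the documents do not allow that to be shown.

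3. **The overall aim concerns associations, not prevalence, and Table 2 collects household size and marital status at both sites.** This stands for regression coefficients, where adjustment may reduce the bias. It does not repair means, prevalences or unadjusted city contrasts. Multilevel terms for site or neighbourhood do not correct selection within addresses. Household size is also not k, which counts only listed, eligible and able older adults.

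4. **The numbers are assumed.** This stands. The result depends mainly on the assumed outcome difference and much less on the household mix.

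A reader might also infer that people living alone are over-represented. The documents do not support that: a sole listed older adult may live with younger adults, or with an older person who was removed from the list.

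**Conclusion.** The statement is inaccurate for Singapore and needs correcting: it is contradicted by the article's own sampling sections. Over-representation of sole listed older adults among those selected follows from the design. If at most two older adults are listed per address and 20–60% of addresses have two, it amounts to 13 to 17 percentage points.

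The consequence for results is conditional. If Singapore descriptive estimates or city contrasts are left unweighted, outcomes related to household composition may be biased at that site only. The shift ranges from nil to about 2 standard errors of the city comparison for assumed differences of 0 to 0.5 SD, ignoring clustering.

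Two stronger conclusions are tempting. One is that the planned loneliness results or the city comparison are biased. The documents state neither the household mix, nor how loneliness varies with it, nor that weights will be omitted. The other is that weighting by k would make the Singapore sample representative of everyone aged 65 or older. It would not, because the upper age limit, the exclusions and the refusals remain.

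**What to change.** - **Wording.** Correct the sentence under *Strengths and limitations of the study*: Berlin is a person sample from the registration office, and Singapore is an address sample from the Department of Statistics with one older adult chosen per address. Say that selection probabilities in Singapore differ with the number of listed older adults.
- **Data.** Retain k, the count on the interviewer's list after removals, as a field for every address. Without it, the weight cannot be built exactly later.
- **Means, prevalences and city comparisons.** Use k, trimmed if needed, as the within-address design weight for Singapore, with robust standard errors. If weights are trimmed, show the untrimmed result as a sensitivity analysis.
- **Association models.** Adjust for household composition and report the k-weighted version as a sensitivity analysis. Weighting every association model as the primary approach is a debatable choice and is not required here.
- **Limits.** State that the weight corrects only within-address selection.

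The cost is one retained field, a few sentences and some precision: under the assumptions above, a design effect of about 1.09 to 1.12, or an effective n of 934 to 960 out of 1,050. Recruitment and the sampling procedure do not change.
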